## Abstract

**Background:** In many cases of pancreatic adenocarcinoma (PDAC), the diagnosis comes as a surprise to the patient, who often faces a disease that is already at an advanced stage, with poor prognosis. The clinical visit during which the diagnosis is communicated together with the first information regarding the planned treatments is of paramount importance. We hypothesize that the clarity of such information can influence patients' engagement and thus their level of compliance.

**Aims:** This study aims to collect (a) quantitative data on the level of PDAC patient engagement, (b) data on the rate of understanding of the information received from the doctor, and (c) data on level of compliance; the possible associations between these variables will be analyzed.

**Methods:** This is a single-center, observational, cross-sectional cohort study on patients diagnosed with PDAC, approved by the Ethics Committee of the San Raffaele Hospital. As no preliminary data are available on the association between PDAC patients' understanding rate and their level of engagement and of compliance, no power calculation is possible. This is a pilot study, aimed at enrolling at least 45 PDAC patients during a period of 3 months.

**Conclusion:** COMMUNIcation and Patient Engagement at Diagnosis of PAncreatic CAncer (COMMUNI. *CARE*) will be the first study specifically investigating whether there is a relation between PDAC patients' engagement, rate of understanding at the time of diagnosis, and compliance.

## Introduction

### Background

Pancreatic ductal adenocarcinoma (PDAC) is a lethal disease with a standardized incidence rate by age of 4.8 and a standardized mortality rate of 4.4 per 100,000 persons worldwide (1). During the last decades, the prognosis of most common cancer types has dramatically improved, but this is not the case of PDAC. Indeed, despite recent improvements, PDAC 5-years survival rate is only ~8% (2). This is because the majority of PDAC patients show unspecific symptoms, and the diagnosis is usually made only at an advanced stage of the disease (3). In addition, no population screening program is available (4). More than 450,000 patients are diagnosed with PDAC worldwide every year, with a significant burden for the health and socioeconomic systems.

The diagnosis of PDAC in most cases is completely unforeseen by the patient, who faces the disease suddenly, often already at an advanced stage, and without a progressive approach to it. The clinical interview in which the diagnosis and the first information regarding treatment options and prognosis are communicated, therefore, is a key moment.

Doctor–patient communication is considered “time of care,” as stated by the Italian law n.219/2017 (5). In light of that, correct communication is an integral part of the care itself and lays the foundations for the construction of the therapeutic alliance between the treating physician and the patient, which is essential to guarantee compliance with the proposed treatments. There are, however, few studies conducted on doctor–patient communication in cancer patients (6) and none specifically on PDAC patients.

Many recent studies claim that a good level of patient engagement is an essential condition to build a solid therapeutic alliance (7, 8); in this regard, objective measurement scales of the patient engagement level have been developed and have been demonstrated to be useful tools to quantify the patient's involvement within the care process (9, 10). Among them is the Patient Health Engagement Scale (PHE-S®), a recently validated assessment scale of simple and non-invasive use, which requires only the administration of a questionnaire (11).

### Hypothesis

The hypothesis to be tested is that clarity of communication between the treating physician and the patient at the time of diagnosis, and the patient's level of understanding of the information received, influences a patient's engagement and compliance with the care process.

### Aims

This study aims to (1) collect quantitative data about the level of PDAC patients engagement and their rate of understanding of the received information and (2) investigate the association between engagement and rate of understanding and of these two variables with the level of compliance.

## Methods and Analysis

### Study Design

This will be a monocentric cohort study (observational, cross-sectional) on PDAC patients.

### Patients

Consecutive outpatients visited by three expert physicians at the Gastroenterology, Pancreatic Surgery and Oncology Clinics of the Pancreas Translational and Clinical Research Center, IRCCS San Raffaele, Milan (Italy) will be considered includable if they meet the following conditions:
adult patients (≥18 years)of Italian mother tonguehave a histological diagnosis of PDAC obtained during the 4 weeks prior to the visitthe visit is their first visit, after completion of diagnostic procedures and is the occasion in which diagnosis and/or treatment strategies are communicatedgive full, written, informed consent.

The following exclusion criteria will be applied:
PDAC recurrence after previous diagnosis and treatmentpoor performance status [Eastern Cooperative Oncology Group (ECOG) ≥ 3].

### Variables

The following variables will be recorded in a dedicated Case Report Form (CRF): age, sex, region of origin, educational level of the patient, habits such as smoking and alcohol intake as previously reported (12), date of the histological diagnosis of pancreatic adenocarcinoma, its stage, and the proposed treatment plan.

The level of patient engagement will be evaluated through the PHE-s® (see Appendix 1).

The rate of understanding of the information received from the patient by the doctor will be determined during a semistructured interview (see Appendix 2) by comparing the number of information conveyed by the doctor with the number of information received/correctly understood by the patient.

The compliance with treatments will be defined as the rate of treatments received compared to what was proposed and planned by the treating physicians and was considered possible by the medical team in light of patient's conditions and side effects.

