### Outcomes

The association between the level of engagement, as evaluated by the PHE-s®, and the patient's rate of understanding during the diagnostic interview, will be assessed to evaluate whether the degree of clarity of the information provided by the doctor influences the level of patient engagement.

The association between the level of patient engagement is calculated with the PHE-s® and patient's estimated rate of understanding according to the interview and the adherence to proposed treatments (compliance).

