### Description of the Intervention (Schedule of Visits)

The study requires (i) the completion of the scheduled outpatients visit with a gastroenterologist, surgeon, or oncologist with strong expertise in PDAC, (ii) the filling of the PHE-S® questionnaire by the patient to investigate the level of engagement, and (iii) the completion of a semistructured interview to assess the rate of understanding of the information received from the doctor.

In more detail:
The treating physician will inform the patient about the study before starting the outpatient visit and communicating information on PDAC diagnosis and planned treatments. The treating physician will also ask permission to the patient regarding the presence during the visit of an external observer (a Ph.D. student in philosophy of language and communication), who will take notes regarding the information provided and will record the audio of the visit if the patient gives further (optional) consent.After the visit, the external observer will ask the patient further written informed consent to use the data collected during the interview and to complete the study. Informed consent forms are presented at this stage rather than at a preliminary stage to avoid anticipating the diagnosis of PDAC, which the patient might not have yet received from the doctor.The patient will be asked to fill in the PHE-s® questionnaire, which takes ~10 min to be completed. PHE-s® is a standardized and validated tool to measure patients' psychological readiness to engage in patients with different medical disorders.The external observer will conduct a semistructured interview of ~30 min to ask the patient questions concerning the clarity of the communication he had received from the doctor and the type of language used, to record the rate of understanding of the information. This phase will ideally take place following the PHE-s® questionnaire, but the patient will be free to postpone it to another moment or day given the possible difficulties for the patient to face an interview immediately following the communication of the diagnosis. The interview will be conducted by an expert observer in the field of language and communication (a Ph.D. student in philosophy of language and communication). The object of the interview is the language used by the treating physician and its clarity for the patient.

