### Statistical Analysis

Categorical variables will be compared using Fisher or chi-square tests and continuous variables using *t* test or Mann–Whitney tests, as appropriate. Subgroups with different levels of engagement will be compared for variables such as sex, age, education, geographic area, stage of disease, type of proposed treatment, and other available data. The PHE-s® questionnaire provides continuous data. The possible correlation of the level of engagement with the clarity of the received information that will be considered as a categorical variable divided in quartiles and with the compliance with treatments will be tested by a Pearson test. Two different univariate and multivariate logistic regression analyses will be run considering patient engagement and compliance as outcome variables and patients' and disease features and the clarity of communication as explanatory variables.

The “enter” method will be employed including all variables that had resulted to be significant at the univariate analysis. Tests of statistical significance and confidence intervals will be two-sided; a *p* < 0.05 will be considered to be statistically significant. A dedicated software (Medcalc 12.1, Belgium) will be employed.

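### The understanding rate makes no allowance for what the patient knew before the visit, so its association with engagement may be confounded by prior knowledge, by an unknown amount

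*Protocol article*

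**What the plan says.** **Definition.** Under Variables, the rate of understanding is determined in a semistructured interview (Appendix 2, not shown) "by comparing the number of information conveyed by the doctor with the number of information received/correctly understood by the patient". The text describes no deduction for items known beforehand and no assessment of knowledge before the visit.

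**Who is enrolled.** Under Patients, histology may be up to 4 weeks old. The qualifying visit may convey the diagnosis, the treatment strategy, or both. The Schedule of Visits places written consent after the visit "to avoid anticipating the diagnosis of PDAC, which the patient might not have yet received from the doctor". Both informed and uninformed patients are therefore expected.

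**What is recorded.** The CRF list under Variables includes "date of the histological diagnosis of pancreatic adenocarcinoma, its stage, and the proposed treatment plan", but not whether or when the patient was told. The Statistical Analysis section does not name prior knowledge among its variables. Its multivariate models enter the variables that were significant in univariate analysis.

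**How the result is read.** The Outcomes section relates PHE-s to the understanding rate "to evaluate whether the degree of clarity of the information provided by the doctor influences the level of patient engagement". The Discussion says that support for the hypothesis would lead to action on the clarity of clinical communication.

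**The concern.** The rate stands in for how clearly this doctor communicated at this visit. A patient who arrives knowing the diagnosis can be credited for diagnosis items that the doctor merely repeats, and that part of the score says nothing about the clarity of the visit.

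Prior knowledge could also be related to the other variable. PHE-s is described thus: "PHE-s® is a standardized and validated tool to measure patients' psychological readiness to engage". A patient who has had days or weeks to absorb the diagnosis may be more ready to engage, or less. If so, prior knowledge moves both variables. A positive link would push the correlation up. A negative link would push it down and could hide a true positive association. Either way, the reading in the Outcomes section would be wrong to that extent. If the information is not collected at enrolment, no later analysis can reliably recover it.

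**Working it through.** The protocol gives no effect size, power or bias figure, so there is nothing of its own to reproduce.

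**Inputs from the article:** 45-60 patients (Power Size Calculation); Pearson test, two-sided, 5% level (Statistical Analysis).

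**Assumed inputs, none from the article:** 10 items conveyed, k of them diagnosis items; each patient's probability of understanding an item has mean 0.60 and SD 0.12; an informed patient is credited with a diagnosis item with probability 0.95; a share q of 25% or 50% already informed; PHE-s higher by d SD in informed patients; no true link between understanding and engagement.

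**Step 1, one illustration.** Two patients hear the same 10 items, 5 on the diagnosis, and each grasps 3 of the 5 treatment items. The uninformed patient grasps 3 diagnosis items: (3+3)/10 = 6/10. The informed patient is credited with all 5: (5+3)/10 = 8/10. Their understanding of the treatment part is identical.

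**Step 2, inflation of the rate.** Inflation = (k/10) × (0.95 − 0.60).
- k=1: 0.1 × 0.35 = 3.5 percentage points
- k=3: 0.3 × 0.35 = 10.5 points
- k=5: 0.5 × 0.35 = 17.5 points

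**Step 3, spurious correlation by hand** for k=5, q=0.5, d=0.8. Covariance = q(1−q) × d × inflation = 0.25 × 0.8 × 0.175 = 0.035. SD of PHE-s = √(1 + 0.25 × 0.64) = 1.077. For the rate, E[p(1−p)] = 0.6 − 0.36 − 0.0144 = 0.2256.
- Variance, uninformed: 0.2256/10 + 0.0144 = 0.0370
- Variance, informed: (5 × 0.2256 + 25 × 0.0144 + 5 × 0.0475)/100 = 0.0173
- Total: average 0.0271 plus between-group 0.25 × 0.175² = 0.0077, giving 0.0348; SD 0.186

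Hence r ≈ 0.035/(1.077 × 0.186) ≈ 0.17. The critical |r| is 0.294 at n=45 and 0.254 at n=60.

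**Step 4, simulation** (20,000 studies per setting, rate kept continuous):

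| Setting | Mean r | Rejection, n=45 | Rejection, n=60 |
|---|---|---|---|
| d=0, any k | about 0 | about 5% | about 5% |
| k=1-2, d=0.5-0.8 | 0.02-0.07 | about 5-8% | about 5-8% |
| d=0.2, k up to 5 | up to about 0.05 | about 5-6.5% | about 5-6.5% |
| k=3-5, d=0.5-0.8 | 0.05-0.17 | about 6-20% | about 6-26% |

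The upper end of the last row is k=5, q=50%, d=0.8. With d=−0.8 the correlation mirrors to about −0.17, with the same rejection rates.

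**Step 5, other assumptions.** A second simulation (2,000 runs per cell) used q=50%, full credit for known items, understanding probability 0.5 or 0.7 with SD 0.15, and d=0.5 or 1. One known item gave 5-7% rejection, three gave 7-24% and five gave 9-52%. In its most extreme cell at n=60, cutting the rate into quartiles as the plan intends lowered rejection only from 52% to 48%.

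**Step 6, effect of adjusting.** In the step 4 settings, the partial correlation given a yes/no indicator of prior knowledge has mean about 0, and its test rejects in about 5% of studies in every setting. This assumes that the indicator is reported correctly.

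**The case against.** **The instrument is not visible.** Appendix 2 may ask what the patient already knew. This stands as a condition on the fix. Even so, the definition under Variables would not use the answer, and no named covariate would carry it.

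**The wording ties the score to the conversation.** A reader might infer that the rate credits every item a patient can state, whatever its source. The text does not say that: it speaks of information received and correctly understood. What stands is narrower. No step described in the article can tell an item learned at the visit from one known before, since knowledge is assessed only afterwards and "the patient will be free to postpone it to another moment or day".

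**The denominator holds only conveyed items.** If an informed patient's visit covers treatment alone, diagnosis items are not counted and cannot inflate the rate through this route. This stands: the problem needs the doctor to repeat diagnosis items.

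**The magnitude is assumed throughout.** This also stands. The article gives no item count, no share of informed patients, and no size or sign for a link to PHE-s. With one or two known items, or a small PHE-s difference, the effect is close to nothing.

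**It is a pilot.** True, and this limits the seriousness. But the pilot's result is meant to decide whether action follows, and the missing piece of information is cheap to collect.

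**Conclusion.** The point holds in a limited form. The rate does not allow for prior knowledge, the study expects patients who differ in it, and nothing named in the text records or adjusts for it. Where diagnosis items are repeated to informed patients, the rate is partly a measure of what they already knew. This matters for the stated inference only if prior knowledge is also related to PHE-s, which is plausible but not documented, and whose direction is unknown.

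The size is unknown. It runs from none (no link to engagement), through about 5-8% rejection (1-2 known items in 10), to about 20% at n=45 or 26% at n=60 (5 known items, half informed, 0.8 SD). More extreme assumptions go higher.

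A reader might infer that an association found in this study would be an artefact of prior knowledge. The document does not support that: it only leaves this explanation open and uncheckable. It is a worthwhile, low-cost improvement.

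**What to change.** Unless Appendix 2 already does so:

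1. Ask in the post-visit interview whether the patient already knew the diagnosis before this visit (yes/no), and add the field to the CRF. Asking afterwards respects the reason for late consent, namely a diagnosis "which the patient might not have yet received from the doctor".
2. Keep the all-items understanding rate as defined.
3. Include prior knowledge as a prespecified covariate in the engagement and compliance models, whatever its univariate p-value. The current selection rule could drop a real confounder in a sample this small.
4. Report the engagement-understanding correlation adjusted for prior knowledge (partial correlation) beside the crude one.

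**Cost:** one question in an interview of about 30 minutes, one CRF field, two sentences in the analysis section, and one degree of freedom among 45-60 patients. The answer is self-reported after the visit, perhaps on a later day, so misreporting would leave some confounding.

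Rescoring on newly learned items only is not recommended as the main analysis. A yes/no answer cannot show which items were known, so it would need item-by-item recall. It would also change the quantity measured, since the Hypothesis section concerns understanding of the information received as well as clarity. Drop it or keep it as an optional sensitivity analysis.

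### No planned analysis relates engagement to compliance while accounting for planned treatment type, so the pooled Pearson correlation can partly reflect modality

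*Protocol article*

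**What the plan says.** Variables defines compliance as one rate for all patients: "The compliance with treatments will be defined as the rate of treatments received compared to what was proposed and planned by the treating physicians". The sentence goes on to limit the comparison to treatment that "was considered possible by the medical team in light of patient's conditions and side effects". No distinction by type of treatment is made.

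Patients recruits from "Gastroenterology, Pancreatic Surgery and Oncology Clinics". Disease stage is not restricted; the exclusions are recurrence and ECOG 3 or worse. The Medication of the Study says that no treatment is preset.

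The case report form records "its stage, and the proposed treatment plan".

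Statistical Analysis uses this information in one explicit place: "Subgroups with different levels of engagement will be compared for variables such as sex, age, education, geographic area, stage of disease, type of proposed treatment". The association of engagement "with the compliance with treatments will be tested by a Pearson test", with no stratification or adjustment. A logistic regression with compliance as outcome takes "patients' and disease features and the clarity of communication as explanatory variables". Only variables significant at univariate analysis go forward to the multivariate step.

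The associations of engagement and of understanding with compliance are stated under both Aims and Outcomes.

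**The concern.** The rate pools patients whose plans differ in kind. A plan with one counted item can only score 0 or 1, while a plan with several can score values in between. Average compliance may also differ between treatment types for reasons unrelated to how engaged the patient is. Treatment type follows stage and prognosis, which could plausibly influence engagement at the diagnostic visit. If both links exist, a pooled correlation between engagement and compliance can appear with no association among patients on the same kind of plan.

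The Discussion says that a supportive result would lead to action on the clarity of clinical communication. A correlation produced by case mix would be a poor basis for that.

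**Working it through.** **The plan's own figure.** Power Size Calculation gives a feasibility figure only: some 500 new patients a year and 45 to 60 enrolled in 3 months. 500/4 = 125 per quarter, so 45/125 = 36% to 60/125 = 48% would have to be eligible and consent. The article gives no such fraction, so the figure can be neither reproduced nor refuted. The point does not depend on it beyond n = 45 to 60.

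**Which planned analysis could give the adjusted association?**

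- Pearson test: relates engagement to compliance, without treatment type.
- Comparison of engagement subgroups: relates treatment type to engagement, without compliance.
- Regression with compliance as outcome: engagement is not among the named explanatory variables. Treatment type is not named either. It could enter as a disease feature, but only after passing p < 0.05 at univariate analysis, which a real confounder can easily miss with 45 to 60 patients.
- Regression with engagement as outcome: the same named explanatory variables, and compliance is not among them.

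None of the four gives it. For understanding and compliance the position is better, because clarity is named in the compliance model, but adjustment for treatment type is still not assured.

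**Size by formula (all inputs assumed).** Let a share p of patients have modality A, let mean compliance differ by D between modalities with within-group SD s, and let engagement differ by d SD. With no association within modality,

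r = [D√(p(1−p)) / √(D²p(1−p) + s²)] × [d√(p(1−p)) / √(d²p(1−p) + 1)].

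Take D = 0.97 − 0.80 = 0.17, s = 0.15 and d = 0.5:

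- p = 0.5: (0.085/√(0.085² + 0.15²)) × (0.25/√1.0625) = 0.493 × 0.243 = 0.12.
- p = 0.2: (0.068/√(0.068² + 0.15²)) × (0.20/√1.04) = 0.413 × 0.196 = 0.08.

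**Size by simulation (all modality inputs assumed).** 2,000 runs per setting; n = 45 or 60; 20% or 40% of patients with a single-event plan scored 0/1, mean 0.80 or 0.95; the rest with 6 planned units, mean 0.70 or 0.85; engagement higher by d SD in the single-event group; no association within modality. Ranges are over the 16 settings at each d.

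| d (SD) | mean spurious r | false positives, unadjusted Pearson | false positives, adjusted for modality |
|---|---|---|---|
| 0 | -0.005 to 0.008 | 4.5% to 5.7% | 4.3% to 5.5% |
| 0.3 | -0.016 to 0.076 | 4.6% to 9.1% | 4.3% to 5.3% |
| 0.5 | -0.018 to 0.115 | 5.0% to 13.3% | 4.3% to 5.9% |
| 0.8 | -0.026 to 0.181 | 5.6% to 28.6% | 4.7% to 5.5% |

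The simulation error at a true 5% is √(0.05 × 0.95/2000) = 0.5 percentage points, so the first row is compatible with 5%. The clearly negative values arise where the single-event group has the lower mean compliance (0.80 against 0.85).

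**Scale.** The correlation detectable with 80% power at two-sided 0.05 is tanh(2.80/√(n−3)): 0.41 at n = 45 and 0.35 at n = 60.

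**The case against.** Four objections carry weight.

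*The contrast is inferred.* A reader might take the article to pool a single operation with many chemotherapy administrations. It names neither as a counted treatment and does not state the counting unit, which a journal article may leave to the full protocol. This stands, so the point cannot rest on that contrast. What the article does state is one rate, varying types of proposed treatment, and an unadjusted test.

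*The denominator is limited to feasible treatment.* The clause on what the team considered possible removes some shortfall that is not patient behaviour, and so may narrow the gap in compliance between modalities. This also stands, and it argues against the larger assumed gaps. It does not make the rates comparable in scale.

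*Unequal variance proves nothing by itself.* With 0.90 adherence per item and independent items, the variance of the rate is 0.09 for one planned item and 0.09/12 for twelve, a 12-fold ratio. A reader might infer a spurious result from that. The first row of the table shows otherwise: with no engagement difference between modalities, the test holds its level.

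*Treatment type is not ignored.* It is recorded and compared across engagement subgroups, which could reveal half of the confounding path. True, but seeing a difference in engagement does not adjust the association with compliance.

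It is also fair to say that this is a pilot, and that the spurious correlations are small beside the 0.35 to 0.41 it could detect with 80% power.

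**Conclusion.** The point holds as a gap in the analysis. The article fixes both the pooled compliance rate and the unadjusted test, and no analysis it describes gives the engagement-compliance association adjusted for planned treatment type.

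The consequence is conditional. Bias needs treatment type to be related to both engagement and compliance, and the documents give no data on either link. Under the assumed ranges it is small to moderate and its sign is uncertain. The upper end needs a 0.8 SD engagement difference, 40% single-event plans and a compliance gap of 0.95 against 0.70. The documents do not support saying that the result will reflect modality, only that it can and that the plan could not tell. The change is worth making because it is nearly free.

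**What to change.** Keep all 45 to 60 patients. Report the engagement-compliance and understanding-compliance associations adjusted for, or stratified by, the planned treatment type, whatever its univariate p-value. Name engagement as an explanatory variable in the compliance model. Report the unadjusted Pearson result alongside.

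Compliance by modality may be shown descriptively: graded where the plan has several administrations, yes/no where it has a single event. The main analysis should not be restricted to patients planned for systemic treatment. If half the cohort were left out, n would fall to about 22 to 30 and the detectable correlation would rise to about 0.57 to 0.49. The aim, which concerns these patients generally, would also be narrowed.

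The cost is wording plus one or two degrees of freedom, since the treatment plan is already in the case report form. With two degrees of freedom spent, the detectable correlation becomes tanh(2.80/√(n−5)): 0.416 instead of 0.407 at n = 45, and 0.361 instead of 0.355 at n = 60. No visit and no aspect of care changes.
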